## Abstract

Despite a number of prospective registries conducted in past years, the current epidemiology of interstitial lung diseases (ILD) is still not well defined, particularly regarding the prevalence and incidence, their management, healthcare utilisation needs, and healthcare-associated costs. To address these issues in Germany, a new prospective ILD registry, “Exploring Clinical and Epidemiological Characteristics of Interstitial Lung Diseases” (EXCITING-ILD), is being conducted by the German Centre for Lung Research in association with ambulatory, inpatient, scientific pulmonology organisations and patient support groups. This multicentre, noninterventional, prospective, and observational ILD registry aims to collect comprehensive and validated data from all healthcare institutions on the incidence, prevalence, characteristics, management, and outcomes regarding all ILD presentations in the real-world setting. Specifically, this registry will collect demographic data, disease-related data such as ILD subtype, treatments, diagnostic procedures (e.g., HRCT, surgical lung biopsy), risk factors (e.g., familial ILD), significant comorbidities, ILD managements, and disease outcomes as well as healthcare resource consumption. The EXCITING-ILD registry will include in-patient and out-patient ILD healthcare facilities in more than 100 sites. In summary, this registry will document comprehensive and current epidemiological data as well as important health economic data for ILDs in Germany.

## 1. Introduction

Interstitial (or diffuse parenchymal) lung diseases (ILDs) represent a large, heterogeneous group of more than 200 different entities, most of which are classified as rare diseases [1–3]. They are defined as lung diseases that affect the alveolar structures, the pulmonary interstitium, and small airways. A diagnosis of an ILD relies mainly on the combination of clinical, radiological, and pathological criteria, which should be explored in a multidisciplinary board. Among the ILDs, the most important are sarcoidosis, idiopathic pulmonary fibrosis (IPF), hypersensitivity pneumonitis (HP), also called extrinsic allergic alveolitis (EAA), ILD as a manifestation of connective tissue disease (CTD), and drug-induced ILD and pneumoconiosis [2, 3]. The majority of ILDs are idiopathic and include the group of idiopathic interstitial pneumonias (IIPs) (Figure 1). Only about one in three cases of ILD have an identifiable cause [1].

Despite being rare diseases, the recent Global Burden of Disease Study reported that interstitial lung diseases rank in 40th position of all diseases regarding global years of life lost in 2013, which represents an increase of 86% compared to 1990 [4]. The most common ILD, IPF, has a poor prognosis with median survival of 2-3 years from diagnosis [5]; for other forms of ILD, prognosis depends on the underlying and/or accompanying disease(s) but may be similarly poor. For example, recent data on sarcoidosis, which is usually considered a more benign ILD, indicates a considerably higher mortality rate than previously reported [6]. Much remains unknown or debatable for many ILDs because there is a lack of data on the prevalence, incidence, and mortality rates of this group of lung diseases as well as clinical evidence guiding optimal management, healthcare utilisation, and their associated healthcare costs [1].

## 2. Current Epidemiological Estimates for ILDs in the US and across Europe

Most data on the epidemiology of ILDs has been derived from prospective registries of data reported by respiratory physicians. However, there are only a few ILD registries and all have limitations due to the difficulties in accurately diagnosing these conditions; many may not therefore be fully representative of the true populations of ILD patients [1].

One of the first published ILD registries was conducted by Coultas et al. in Bernalillo County, New Mexico, between 1988 and 1990 [7]. According to this registry, the prevalence of ILDs was 20% higher in males (80.9 per 100,000) than in females (67.2 per 100,000). Similarly, the overall incidence of ILDs was slightly more common in males (31.5 per 100,000/year) than females (26.1 per 100,000/year). The authors concluded that the occurrence of ILDs in the general population may be more common than previous estimates based on selected populations, and these disorders may frequently be unrecognised [7].

ILD registries conducted in Europe include a 2004 registry in Greece, which involved a total of 967 cases indicating a prevalence rate of 17.3 per 100,000 inhabitants and an incidence rate of 4.63/100,000 per year [8]. Two Spanish registries also reported a lower incidence of ILDs. One Spanish ILD registry involved 511 cases with an incidence of 7.6 per 100,000/year and a similar male-to-female ratio [9]. A second Spanish registry in the southern provinces involved 744 cases, of which 40.1% of the diagnoses were biopsy confirmed. This reported an annual incidence of 3.62 cases/100,000 (men 4.18 cases/100,000/year; women 3.07 cases/100,000/year) [10].

However, in a more recent study conducted in Turkey between 2007 and 2009 utilising the ATS/ERS consensus criteria from 2002, the incidence of ILD was more similar to that reported in New Mexico, 24.7 per 100,000 person-years for males and 27 per 100,000 person-years for females [7, 11]. This may therefore be a more accurate estimate of the incidence of ILDs because it is also supported by a UK study concerning both IPF and sarcoidosis [12]. This database of UK general practitioners aimed to identify the incidence and mortality rates of IPF and sarcoidosis and was representative of the general population. In this study, the incidence of IPF was 4.6/100,000 per year and 5.0/100,000 per year for sarcoidosis. This study also found a progressive increase in the incidence of IPF between 1991 and 2003, which was not explained by the ageing of the UK population. Since these two relatively predominant presentations—IPF and sarcoidosis—may represent between one-third and one-half of all ILD cases, this would suggest an ILD incidence of 20–30 per 100,000 person-years [1, 12].

These estimated figures are underpinned by a registry conducted in Denmark between 1995 and 2005 involving 21,765 patients with ILDs based on the ICD-8 and ICD-9 classifications identified through the Danish National Patient Registry [13]. This included all in-patients and out-patients with a corresponding hospital discharge diagnosis. The incidence rate fluctuated during the observation period, decreasing from 27.14 per 100,000 person-years to 19.36 per 100,000 person-years. After 1998 the incidence increased considerably, peaking at 34.34 per 100,000 person-years in 2002 and then subsequently decreasing slightly [13].

### 2.1. Epidemiology of Specific ILDs

A number of registries provided relevant information on the epidemiology of specific ILDs, rather than comprehensively, which has been reviewed by Demedts et al. (2001) [14]. For example, in a registry in Belgium involving a total of 362 cases over a 3-year period (1992−1996), the most frequent diagnosis was sarcoidosis (31%), followed by IPF (20%), allergic pneumonia (13%), and vascular collagen diseases (9%) [15, 16]. Similarly, in a single German ILD registry performed between 1995 and 1999 involving 1142 patients, sarcoidosis and IPF were the most frequently registered ILDs [17, 18].

In many of these registries IPF and sarcoidosis were the most common ILDs (Table 1) [19]. However, since most of these studies were conducted before the introduction of the changes in the most recent classifications, the figures concerning ILD as a whole are probably more reliable than those concerning idiopathic interstitial pneumonias specifically [18]. There are also a number of registries dedicated to specific ILDs, such as the INSIGHTS-IPF registry, which focuses solely on IPF [20].

## 3. Rationale for the EXCITING-ILD Registry

As highlighted previously, the only German ILD registry was performed prior to the former and the current ATS/ERS consensus classification [2, 3] and did not reflect a true population-based registry. In this registry only limited data were collected, focusing on the diagnostic procedure, whereas data regarding disease outcome, prognostic factors, pharmacological and nonpharmacological management, and socioeconomic data were not recorded [17, 18]. Similar to Germany, other ILD registries have mainly collected prospective data from specialised ILD outpatient clinics only or used ICD classification or hospital discharge data. Furthermore, data were collected prior to the recent consensus IIP classification in 2013 [1]. Data from community pulmonologists has been lacking in registries conducted to date, which further complicates interpretation of the impact of ILDs in Germany and across Europe. This is important since current data suggests that ILDs may be underestimated and undervalued. For example, symptoms may be misinterpreted as “normal” symptoms of ageing. In addition, the increasing use of CT imaging for nonpulmonary indications (e.g., cardiac or spinal CT) may mean that more subclinical ILDs are being diagnosed than in the past. Altogether, these factors further compound difficulties in ascertaining accurate, population-based epidemiological data on rare, or very rare, diseases such as many of the ILDs.

Registries are increasingly recognised as important observational studies for collecting “real-world” practice information and enabling prolonged follow-up for longer-term data collection. Furthermore, they can be particularly relevant for benchmarking and quality assurance, as individual centres can compare their results with other centres. To address this issue in Germany, the German Centre for Lung Research (DZL) is conducting a prospective ILD registry in association with ambulatory, in-patient, scientific pulmonology organisations, as well as a patient support group. This multicentre, noninterventional, prospective, and observational disease and outcomes ILD registry aims to collect comprehensive and validated data from all healthcare institutions on the incidence, prevalence, regional distribution, characteristics, management, and outcomes regarding all ILD presentations in the real-world setting. Specifically, this registry will collect demographic data, disease-related data such as ILD subtype, treatment locations, diagnostic procedures (e.g., HRCT, surgical lung biopsy), risk factors (e.g., familial ILD), comorbidities, ILD management, analysed by the type and frequency of pharmacological and nonpharmacological interventions, and disease outcomes as well as healthcare resource consumption. The “Exploring Clinical and Epidemiological Characteristics of Interstitial Lung Diseases” (EXCITING-ILD) registry will include in-patient and out-patient ILD healthcare facilities in 3 German states and involve more than 100 sites with a follow-up of at least 5 years. This registry will document comprehensive and current epidemiological data, as well as important health economic data, for ILDs in Germany.

## 4. EXCITING-ILD Registry Objectives

The overall objective of the EXCITING-ILD registry is to generate sociodemographic and medical data relating to ILDs, which will help to answer epidemiological and disease-related questions that will be important in Germany. This registry will also provide an important database for health economic and health services research questions.

Specific objectives of the EXCITING-ILD registry will be to determineclinical, disease-related characteristics of ILD patients;diagnostic procedures for the identification of ILDs;the clinical management of different (sub)types of ILD in real-world practice;the outcome of different types of ILDs and of ILD-related therapies from all forms of healthcare facilities.

Main endpoints, reflecting the objectives of this registry, areincidence and prevalence of ILD subtypes;(disease-related) characteristics of ILD patients;diagnostic procedures for the identification of ILDs;management of different (sub)types of ILD;the outcome of different types of ILDs and of ILD-related therapies measured as time to death;ILD management as analysed by the kind and frequency of pharmacological and nonpharmacological therapies;prognostic factors in different ILDs;lung functional parameters.

Healthcare utilisation will be assessed as a basis for cost estimates for the following healthcare services:outpatient treatment;hospitalisation due to ILD;temporary occupational disability;medication;additional therapies;medical aids and appliances;participation in rehabilitation programmes.

Sociodemographic data variables aregender;year of birth;country of birth;place of residence;profession;incapacitated for work;health insurance coverage (statutory, private, and granting aid).

## 5. Methods

### 5.1. Study Design and Setting

The EXCITING-ILD registry is a multicentre, noninterventional, prospective, observational disease and outcomes registry across healthcare facilities in Germany. Collected data (retrospective and prospective) will be entered into a web-based system that conforms to the data protection act. The planned duration of the registry is at least 5 years.

### 5.2. Patients and Sites

In the initial 12-month phase it is anticipated that 350 patients will be enrolled and a total of up to 600 patients after the second year. Patients will be recruited in around 100 centres from all forms of healthcare facilities managing ILDs. If comparisons between different ILDs are deemed to be necessary, comparator arms will be defined within the course of the registry, depending on clinical considerations and statistical power.

### 5.3. Inclusion and Exclusion Criteria

The inclusion criteria are adult patients (≥18 years) diagnosed with ILD with signed informed consent and will include the following ILD subtypes (Table 2). Exclusion criteria are patients without ILD.

### 5.4. Study Schedule and Variables

The following data will be collected at baseline and follow-up visits (Table 3). No study-specific patient tests will be performed during this study. Personal data/date of birth/gender will only be recorded once for creation of the anonymous patient identification number.

### 5.5. Patient Withdrawal/Discontinuation

Patient drop-out or withdrawal may occur for the following reasons and will be recorded.

Withdrawal by the investigator due toadministrative reasons;lost for follow-up.

Withdrawal by patient from the study due toown request;specific request of the sponsor.

In the event that a patient is withdrawn, the registry termination page in the eCRF will be completed, including information on the date of the withdrawal, who initiated the withdrawal, and the reason for withdrawal, if known. Reasonable effort will be made to contact any patient lost to follow-up during the course of the registry to retrieve any outstanding data.

### 5.6. Pharmacological and Nonpharmacological Treatment

The registry will document the management and treatment of patients with ILDs in real-life clinical practice. ILD management will be analysed by the type and frequency/usage of pharmacological and nonpharmacological therapies.

Information on the following pharmacological therapies will be documented at baseline and at follow-up, including any changes in treatment with relevant details on dosing:Azathioprine.Prednisone.NAC (N-acetylcysteine).Pirfenidone.Nintedanib.Cyclophosphamide.Methotrexate (MTX).Mycophenolate mofetil (MMF).Rituximab.Inhaled antiobstructive therapy (LAMA, LABA).Inhaled corticosteroids (ICS).Rapamycin/sirolimus.TNF alpha blocker.Clinical trial medication.Other treatment.

Information on the following nonpharmacological treatments will be documented:Physiotherapy or treatment of other allied healthcare professionals.Long-term oxygen therapy.Noninvasive ventilation.Lung transplantation or listed for lung transplantation.Patient support group.Participation in rehabilitation programmes.Others.

### 5.7. Statistical Methods

A Statistical Analysis Plan (SAP) has been developed prior to initiation of the registry and final analysis of the trial will be performed by syneed medidata GmbH. All observational data collected will be analysed descriptively using established statistical and epidemiological methods. Time to death will be analysed by means of Kaplan-Meier survival analysis. In addition, further secondary inferential methods may be specified in the SAP if deemed appropriate. If not specified otherwise in the SAP, missing data will not be imputed. Subjects with incomplete data will be included in the analysis and for each variable; the number of subjects with missing data will be reported. Interim analyses comprising descriptive summaries of the data collected in the CRF will be produced every 3 months.

*Sample Size*. In the initial phase of 12 months, enrolment of up to 350 patients is anticipated. At the end of year 2, it is anticipated that up to 600 patients will be enrolled. This sample size (*n* = 350) allows for a log-rank test at a fixed time given a hazard ratio ≤0.68 at alpha = 0.05 with a power of 95%. Equally, this allows for estimating an event with 50% frequency at a confidence interval of ±5% at a 95% confidence level. All subjects with at least one documented postbaseline visit will be entered into the full analysis set (FAS). Further analysis sets may be defined in the SAP.

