## Figures and Tables

**Figure 1 fig1:**
[figure not shown]
Classification of ILDs. PAP: pulmonary alveolar proteinosis, LAM: lymphangioleiomyomatosis, and PLHC: pulmonary Langerhans cell histiocytosis. Adapted from the American Thoracic Society, European Respiratory Society International Multidisciplinary Consensus Classification of the Idiopathic Interstitial Pneumonias, Am J Respir Crit Care Med. 2002, and Travis et al. Am J Respir Crit Care Med. 2013 [2, 3].

**Table 1 tab1:** Comparison of the distribution of interstitial lung diseases (ILDs) in respiratory physicians' prospective registries [18].

	Flanders (Belgium) (1992–1996)		Germany (1995)	Italy (1997–1999)	Spain/RENIA (1998–2000)	Spain/SEPAR (2000-2001)	Greece (2004)	
	Prevalent cases	Incident cases	Incident cases	Prevalent cases	Incident cases	Incident cases	Prevalent cases	Incident cases
Subjects (*n*)	362	264	234	1138	744	511	967	254
Idiopathic								
Sarcoidosis	112 (31)	69 (26)	83 (35)	344 (30)	87 (12)	76 (15)	330 (34)	60 (23)
IPF/IIP	62 (17)	50 (19)	76 (32)	417 (37)	287 (39)	215 (42)	234 (24)	66 (25)
COP/BOOP	10 (2.3)	9 (3.4)	16 (6.8)	57 (5.0)	38 (5.1)	53 (10)	51 (5.3)	18 (7.0)
(C)EP	9 (2.2)	7 (2.7)		27 (2.3)	—	—	21 (2.2)	7 (2.7)
CTD	27 (7.5)	19 (7.2)	5 (2.1)	—	69 (9.3)	51 (19)	120 (12)	30 (12)
Vasculitis^*∗*^	5 (1.4)	4 (1.5)	2 (0.8)	25 (2.2)	—	—	14 (1.5)	6 (2.3)
EG/HX	13 (3.6)	7 (2.7)	—	73 (7.2)	6 (0.8)	15 (3)	37 (3.8)	7 (2.7)
Nonidiopathic								
EAA	47 (13)	32 (12)	25 (11)	50 (4.3)	38 (5.1)	34 (7)	25 (2.6)	7 (2.7)
Drug^†^	12 (3.3)	12 (5)	6 (2.6)	21 (1.8)		21 (4)	17 (1.8)	4 (1.5)
Pneumoconiosis^‡^	19 (5.0)	18 (6.8)	6 (2.6)	—	55 (7.4)	—	20 (2.0)	8 (3.1)
Variable aetiology								
Nonspecific fibrosis	33 (9.1)	27 (10)	12 (5.1)	—	69 (9.3)	—	82 (8.5)	40 (15)
Others	13 (3.8)	10 (3.8)	—	124 (11)	76 (10)	9 (2)	15 (1.5)	6 (2.3)

Data are presented as *n* (%), unless otherwise stated. RENIA: Registry of Interstitial Pneumopathies of Andalusia; SEPAR: Sociedad Española de Neumología y Cirugía Torácica; IPF: idiopathic pulmonary fibrosis; IIP: idiopathic interstitial pneumonia; COP: cryptogenic organising pneumonia; BOOP: bronchiolitis obliterans organising pneumonia (not necessarily cryptogenic); (C)EP: (chronic) eosinophilic pneumonia; CTD: connective tissue disease; EG/HX: eosinophilic granuloma/histiocytosis X; EAA: extrinsic allergic alveolitis (hypersensitivity pneumonitis).

^*∗*^Goodpasture's, granulomatosis with polyangiitis (Wegener's), Churg-Strauss, and so forth.

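### The 95% log-rank power for n = 350 requires 350 deaths in two equal halves of the cohort; the ILD comparisons the registry foresees would have considerably less

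*Protocol article*

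**What the plan says.** Section 5.7 makes one power statement. It concerns the 350 patients of the first year, a number which, it says, "allows for a log-rank test at a fixed time given a hazard ratio ≤0.68 at alpha = 0.05 with a power of 95" per cent. It does not state the two groups, their relative size, the sidedness of alpha, the proportion expected to die or the fixed time. The endpoint is death: "Time to death will be analysed by means of Kaplan-Meier survival analysis". On later enrolment the same paragraph adds: "At the end of year 2, it is anticipated that up to 600 patients will be enrolled".

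Section 5.2 is the only place that explicitly names a comparison, and it does so conditionally: "If comparisons between different ILDs are deemed to be necessary, comparator arms will be defined within the course of the registry". It then says what the choice will rest on: "comparator arms will be defined within the course of the registry, depending on clinical considerations and statistical power".

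Table 2 lists many eligible subtypes. Table 1 ("Comparison of the distribution of interstitial lung diseases (ILDs) in respiratory physicians' prospective registries") is the article's only evidence on how cases divide among them. Section 4 includes time to death by type of ILD and for ILD-related therapies, as well as prognostic factors, among the main endpoints.

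**The concern.** A log-rank test draws its power from the number of deaths and from how they are divided between the groups. Section 5.7 attaches 95% to a number of patients and gives no split. The figure therefore takes the most favourable value of both quantities without saying so: everyone dies, and the whole cohort falls into two equal groups. The comparison foreseen in 5.2 meets neither condition.

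This matters because 5.2 makes the choice of comparator arms depend partly on power, and 5.7 is the only power figure in the article. Someone choosing arms, or later interpreting a null survival comparison between two ILDs, could take 95% as the relevant figure when the true one may be near or below one half.

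**Working it through.** **Inputs.** From 5.7: n = 350, up to 600 by the end of year 2, HR 0.68, alpha 0.05, power 95%. From Table 1, German column (234 incident cases): sarcoidosis 83, IPF/IIP 76, EAA 25. Death proportions of 50% and 30% are assumptions, applied equally to both groups, because the article gives none for the cohort.

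**Step 1: reproduce the stated figure.** Schoenfeld, two-sided, equal groups:

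D = 4 × (1.960 + 1.645)² / (ln 0.68)² = 4 × 12.995 / 0.14874 = 349.5 deaths.

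With D = 350, power is 95.0%, so the stated n equals the required number of deaths. Freedman's formula gives 359 deaths. One-sided alpha gives 292, which still means 292/350 = 83% of the cohort dead, in equal groups.

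**Step 2: is universal death plausible?** The Introduction gives IPF a median survival of 2 to 3 years from diagnosis, and 5.1 plans at least 5 years. Assuming a constant hazard and five full years from diagnosis, the proportion dead in IPF would be 1 − 0.5^(5/3) = 68% to 1 − 0.5^(5/2) = 82%. The Introduction describes sarcoidosis as usually considered more benign, although it cites higher mortality than previously reported. Nothing in the article supports 100% deaths across the cohort.

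**Step 3: foreseen pairs.** Applying the German shares to 350:

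- sarcoidosis 83/234 × 350 = 124
- IPF/IIP 76/234 × 350 = 114
- EAA 25/234 × 350 = 37

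Sarcoidosis plus IPF/IIP is 238 of 350 patients; IPF/IIP plus EAA is 151.

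Power = Φ(|ln 0.68| × √(D·p·(1−p)) − 1.960), where D is the deaths in the two groups, p is the share in one of them, and |ln 0.68| = 0.3857.

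If all die, with unrounded group sizes:

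- Equal halves of the cohort: D·p·(1−p) = 350 × 0.25 = 87.5, power 95%.
- Sarcoidosis vs IPF/IIP: 124.1 × 113.7 / 237.8 = 59.3; 0.3857 × 7.70 − 1.960 = 1.01, power 84%.
- IPF/IIP vs EAA: 113.7 × 37.4 / 151.1 = 28.1; 0.3857 × 5.30 − 1.960 = 0.09, power 53%.

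Multiplying D by the death proportion gives the other columns:

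| Comparison at HR 0.68, two-sided 0.05 | n = 350: all die | 50% die | 30% die | n = 600: all die | 50% die | 30% die |
|---|---|---|---|---|---|---|
| Whole cohort, equal halves | 95% | 72% | 51% | 99.7% | 92% | 73% |
| Sarcoidosis vs IPF/IIP | 84% | 56% | 37% | 97% | 79% | 57% |
| IPF/IIP vs EAA | 53% | 30% | 20% | 76% | 47% | 31% |

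**Step 4: sensitivity to case mix.** With n = 350 and all patients dead, sarcoidosis vs IPF/IIP ranges from 58% to 84% across the Table 1 registries, and IPF/IIP vs EAA from 20% to 53%. The German mix is at the favourable end for both. A one-versus-rest split does better: IPF/IIP against all other ILDs gives 78% to 94.5% if all die. With the German mix it is 92%, falling to 67% if half die.

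**The case against.** Section 5.7 does not promise 95% power for any pair of ILDs; it refers to an unspecified log-rank test, and the formula does return 95%. Section 5.2 makes ILD comparisons conditional and ties the arms to power, which suggests power would be assessed when the arms are defined. The analysis is mainly descriptive, and the SAP may give the groups. Section 4 also links outcome to therapies and prognostic factors, and a factor recorded on everyone could divide the whole cohort in two. The Table 1 shares come from other registries, the German one dating from 1995, and its IPF/IIP row pools entities that Table 2 separates.

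Most of this stands, and it limits what can be said. A reader might infer that about 84% is the most any ILD comparison could reach. The documents do not support that: the same pair reaches 97% at n = 600 if all die, and 91% at n = 350 with one-sided alpha, whose sidedness the article leaves open. IPF/IIP against the rest reaches 92%, and a hazard ratio below 0.68, which 5.7 allows for, gives more. Conversely, 84% is itself too high once patients survive. A reader might also infer that the registry will never compare two halves of its cohort, or that subtype comparisons will certainly be run as if they had 95% power. Sections 4 and 5.2 leave both open.

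None of this rescues the stated figure. A whole-cohort split by a therapy or prognostic factor would also need about 350 deaths and equal groups. A reference in 5.2 to power gives no guidance when the only power figure stated omits both the deaths and the split on which it depends.

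**Conclusion.** The concern holds in this form: 95% at n = 350 is correct only for 350 deaths in two equal groups, and the comparison the article foresees would not supply them. With German Table 1 shares, HR 0.68 and two-sided alpha, power at n = 350 is about 84% (sarcoidosis vs IPF/IIP) and 53% (IPF/IIP vs EAA) if every patient dies, about 56% and 30% if half die, and about 37% and 20% if 30% die. Allocation and deaths each contribute: unequal partial groups lower power even with universal death, and survival lowers it even with an ideal split (72% at 50% deaths). At n = 600, about 58% of the cohort (349.5/600) would have to die, in equal groups, to reach 95%.

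The subtype shares and death proportions are assumptions, so the pair figures are illustrations and not bounds. That the stated n equals the required number of deaths depends on neither. The consequence is moderate: the registry is mainly descriptive, but the figure bears on a decision that 5.2 explicitly assigns to power.

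**What to change.** In 5.7, withdraw the unqualified 95% for n = 350, or say that it requires about 350 deaths in two equal groups at HR 0.68 with two-sided alpha. Replace it with a small table of power, or detectable hazard ratio, for the ILD comparisons foreseen in 5.2. Compute it from deaths and allocation through D·p·(1−p), at n = 350 and n = 600, over a stated range of subtype shares and death proportions. State the sidedness of alpha and the fixed time. Do not enter 84% as a ceiling, since that would carry the universal-death assumption into the new text. Refer to this table in 5.2 as the basis for deciding on comparator arms, and update it as the registry's own case mix and deaths become known.

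The cost is a reworded paragraph, one table and a less favourable stated power. No extra patients or data are needed.

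### The 95% log-rank power stated for 350 patients needs about 350 deaths, so it holds only if essentially every enrolled patient dies

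*Protocol article*

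**What the plan says.** Section 5.7 (Sample Size) first gives the planned enrolment: "In the initial phase of 12 months, enrolment of up to 350 patients is anticipated", rising to at most 600 by the end of year 2. Section 5.2 repeats the first figure: "In the initial 12-month phase it is anticipated that 350 patients will be enrolled". In both places 350 is a number of patients.

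Section 5.7 then attaches the power to that number, saying that it "allows for a log-rank test at a fixed time given a hazard ratio ≤0.68 at alpha = 0.05 with a power of 95" per cent.

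Three other statements bear on the point:

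- Section 4 lists outcome, measured as time to death, among the main endpoints. Section 5.7 plans Kaplan-Meier analysis for it.
- Section 5.2 leaves comparator arms to be set up during the registry if needed, with statistical power as one of the criteria.
- The only survival figure for a specific disease is in the Introduction, where IPF is said to have a "poor prognosis with median survival of 2-3 years from diagnosis".

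**The concern.** For a given hazard ratio, the information in a log-rank test comes from the deaths. A patient still alive at the analysis adds follow-up time but no event. A power statement that gives only a number of patients therefore implies some proportion dying, and here that proportion turns out to be about 100%.

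This sentence is the article's only power statement for a comparison of survival. If comparator arms are later chosen partly on power, a reader who takes it at face value would think that 350 enrolled patients are enough to detect a hazard ratio of 0.68. With realistic numbers of deaths they may be far from enough, and a non-significant result would then say little.

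**Working it through.** **Inputs from Section 5.7:** 350 patients, hazard ratio (HR) 0.68, alpha 0.05, power 95%, endpoint time to death. **Assumed, because the article does not say:** two equal groups (the most favourable split), two-sided alpha, no loss to follow-up. Other choices are tried below.

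**1. Reproducing the plan's figure.** Schoenfeld, equal groups:

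d = 4 (z₀.₉₇₅ + z₀.₉₅)² / (ln HR)² = 4 (1.960 + 1.645)² / (ln 0.68)² = 4 × 12.995 / 0.1487 = 349.5, rounded up to 350 deaths.

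The stated pair (350, 95%) comes back exactly, but with 350 as deaths. Power at 350 deaths is 0.950.

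**2. Other readings of the same inputs**

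| Reading | Deaths needed | Against 350 patients |
|---|---|---|
| Schoenfeld, two-sided, 1:1 | 350 | 100% must die |
| Schoenfeld, one-sided, 1:1 | 292 | 83% must die |
| Freedman, two-sided, 1:1: 12.995 × (1.68/0.32)² = 358.2 | 359 | more than enrolled |
| Schoenfeld, two-sided, 1:2 | 394 | more than enrolled |
| Schoenfeld, two-sided, 1:3 | 466 | more than enrolled |

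Reading 350 as the size of each group would mean 700 patients, which is above the planned maximum of 600.

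**3. Power by proportion dying.** Power = Φ(|ln 0.68| × √(d/4) − 1.960). Example with 105 deaths: 0.3857 × √26.25 = 1.976; 1.976 − 1.960 = 0.016; Φ(0.016) = 0.506.

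| Share who die (assumed) | Deaths, n = 350 | Power | Deaths, n = 600 | Power |
|---|---|---|---|---|
| 20% | 70 | 0.364 | 120 | 0.561 |
| 30% | 105 | 0.506 | 180 | 0.735 |
| 50% | 175 | 0.723 | 300 | 0.916 |
| 100% | 350 | 0.950 | 600 | 0.997 |

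With 600 patients, 350 deaths correspond to 350/600 = 58% mortality.

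**4. A pessimistic-survival check from the article's own figure.** Suppose every patient had IPF, survival were exponential with median 2 or 3 years in one half and HR 0.68 in the other half, and everyone were followed for 5 years.

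- Median 2 years: rate ln 2/2 = 0.347 per year. Deaths by 5 years are 82.3% in one half and 1 − exp(−0.68 × 1.733) = 69.2% in the other, on average 75.8%. That is 265 deaths of 350, power 0.88.
- Median 3 years: 68.5% and 54.4%, on average 61.5%. That is 215 deaths of 350, power 0.81.
- The same model with 600 patients gives 455 and 369 deaths, power 0.98 and 0.96.

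**5. Detectable HR with 105 deaths (30% of 350).** 80% power: exp(−(1.960 + 0.842)/√26.25) = 0.58. 95% power: exp(−3.605/√26.25) = 0.495, about 0.50.

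**The case against.** The strongest reply is that little hangs on the sentence. All data are to be analysed descriptively, inferential methods are secondary and optional, no comparison is defined, and enrolment is only anticipated. Power is also to be considered when arms are defined, so this sentence does not settle it. That stands, and it limits the seriousness of the error. It does not make the figure correct.

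A second reply is that an article need not give mortality, allocation or sidedness. That also stands: their absence is not counted as a fault here. The fault is that a specific power is stated for a number of patients that does not provide it.

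Several stronger readings are tempting but not supported:

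- *The registry can never reach 95%.* This does not follow. Step 4 falls short for 350 patients at 5 years. Up to 600 patients are planned, with follow-up of at least 5 years, and 600 all-IPF patients could exceed 95%. However, the cohort takes all ILD subtypes, including sarcoidosis, which the Introduction describes as usually considered more benign, and the sentence rests on 350.
- *"given a hazard ratio ≤0.68" makes the figure a best case.* The reverse is true. 0.68 is the hardest effect in that range; HR 0.60 would need about 199 deaths and HR 0.50 about 108.
- *The reference to a fixed time is itself an error.* It can mean a fixed analysis date or a fixed length of follow-up, either of which is legitimate.
- *Power for a particular pair of diseases, scaled from Table 1, shows the true loss.* No such pair is planned, and the German column is an old case mix from a registry that Section 3 says was not truly population-based.
- *An event count was certainly mislabelled.* The exact match makes this likely, but no formula is shown. The conclusion does not depend on it.

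**Conclusion.** The power statement is wrong as written. At HR 0.68 with two equal groups, 95% power takes about 350 deaths two-sided or 292 one-sided. For 350 patients this means that essentially all, or 83%, must die before the analysis. None of the other readings tried makes it hold at a lower mortality than that.

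The size of the shortfall cannot be fixed from the article, because it gives no cohort mortality. Under the assumed 20% to 50% mortality, power is about 36% to 72%. In an all-IPF cohort followed for 5 years it is about 81% to 88%. These figures assume a 1:1 split, two-sided alpha and no loss to follow-up. Unequal groups or dropout would lower them.

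This should be corrected, but it does not undermine the descriptive aims of the registry, and no pre-specified test depends on it.

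**What to change.** Reword the power sentence in Section 5.7, and in the full protocol and SAP if they carry it:

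- State that about 350 deaths, in two groups of equal size, give 95% power for HR 0.68 at two-sided alpha 0.05.
- Under a stated mortality assumption, give the power or the detectable HR for the deaths expected at 350 and at 600 patients. For example, 30% mortality at n = 350 means 105 deaths, with a detectable HR of about 0.58 at 80% power and about 0.50 at 95%.
- In Section 5.2, say that the power judgement for any later comparator arms will use the deaths accrued and the actual group sizes, not enrolment.

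The cost is one paragraph of text. No extra patients or data are needed. The stated power will look less favourable.
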